The sample size was calculated based on the primary outcome measures (potentially modifiable risk factors for falls, especially motor risk factors). The sample size was calculated using the statistical program G*Power 3.1, assuming (1) the purpose of identifying the effectiveness of risk factors after 16 weeks of intervention; (2) the test used (two-way ANOVA, considering group and time effects, with Bonferroni test to control type I error due to multiple primary outcomes); (3) the main measure; (4) type I error at 5%; (5) statistical power at 80%; and (6) an effect size of 0.25, a minimum of 28 people should constitute the total sample. Furthermore, to verify the sociodemographic and clinical factors that influence adherence and satisfaction, the rule of at least 10 cases of the outcome (success or failure, depending on which is rarer) was used for each independent variable used in the logistic/linear regression model [12]. Thus, considering an adherence of 80% based on a previous study by the research group [9] and the use of univariate regression analyses, a minimum of 50 people should constitute the total sample. With the chance of losing 20% of participants, a sample of 60 people in total is estimated.

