### 2.5. Outcome Measures

Participants will be instructed to wear comfortable clothing and appropriate shoes and use hearing and/or visual aids when necessary. The assessment will be performed at baseline, after 16 weeks of intervention, after 6-month follow-up, and after 12-month follow-up. The evaluators will be blinded and properly trained. All tests will be explained in a clear, simple, and objective manner to the participants. The assessments will be performed at the participants’ homes, if possible, in an environment with minimal noise and distractions.

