### 2.6. Primary Outcome Measures

Primary outcome measures include falls data and potentially modifiable risk factors for falls. A fall will be defined to the volunteer as “an event that results in a person inadvertently coming to rest on the ground or other level below and it is not a consequence of a violent blow, loss of consciousness, sudden onset of paralysis or epileptic seizure” [15]. The number of falls and their consequences (lesion, fracture, death, fear of falling, functional difficulty, expenditure, and others) will be monitored in both groups for 12 months through monthly telephone calls, with third party verification to reduce recall bias. Table 1 presents assessments of risk factors for falls.

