### 2.9. Statistical Analysis

A descriptive analysis will be performed. A significance level of α = 0.05 will be adopted for all analyses and the SPSS (22.0) software will be used to perform the statistical tests. The analysis will be performed by intention to treat. The Kolmogorov–Smirnov normality test will be applied to all continuous variables to verify data distribution. To compare groups regarding clinical and sociodemographic characteristics, the chi-square association test for categorical variables, the independent *t*-test for continuous variables with normal distribution, and the Mann–Whitney test for continuous variables with non-normal distribution will be used.

If the normality hypothesis is rejected, the z-score calculation will be performed to standardize continuous data. Volunteers will be classified as having no clinical improvement when the GRCS score is between −7 and 0, moderate improvement between 1 and 3, and great improvement between 4 and 7 after the intervention. The anchoring technique will be used to estimate the minimum clinically relevant difference, using the GRCS as an anchor. Correlations between the GRCS and performance changes of each test will be conducted. The Receiver Operating Characteristic (ROC) analysis will be used to compare the values of each test between volunteers who improved and did not improve according to the GRCS. Through this method, the cutoff score, specificity, and sensitivity of each test will be analyzed [15].

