To verify the effectiveness of the interventions, the chi-square association test will be used for categorical variables. About the use of fNIRS, a pilot study was conducted before data collection, and the fNIRS signal demonstrated good quality across the targeted channels and participants, with minimal signal loss or saturation. This assured us the feasibility and reliability of the measurements. Regarding the data workflow, motion artifact control, and ROI selection, at this stage, the specific fNIRS data analysis is still ongoing, and a preregistered analysis plan has not yet been developed. We intend to finish this step until the end of 2025. Using the fNIRS, the digitizer data will be entered into the NIRS-SPM software package (v. 4), implemented in MATLAB 2017 (Natick, MA, USA). The fNIRS data will be preprocessed using custom MATLAB algorithms [51]. For quantitative variables, the two-way ANOVA test will be used to verify the interaction between groups and evaluations, with Bonferroni test to control type I error due to multiple primary outcomes. If an interaction is identified, simple main effects analyses will be performed, with adjustments for multiple comparisons (Bonferroni). To verify the proportion of individuals who did not suffer any fall episode during the 12-month follow-up (“proportion of people who did not have the first fall” and “proportion of people who did not have the second fall”), the Kaplan–Meier analysis will be used.

To verify adherence and satisfaction with interventions and sociodemographic and clinical factors that influence them, descriptive analyses of quantitative and qualitative data will be used, using the MAXQDA2022 software for coding and categorization. The excerpts of the responses will be separated into segments containing the ID of each volunteer and their corresponding code. After coding, the segments obtained will be organized using Bardin’s content analysis [52]. Furthermore, simple linear regression analysis will be used to verify possible influences of adherence (frequency) and satisfaction (score). Also, descriptive analyses and the chi-square association test will be used.

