**Figure 4 healthcare-13-01814-f004:**
[figure not shown]
Participant timeline. ** According to SPIRIT checklist, X = task to be performed.

**Table 1 healthcare-13-01814-t001:** Assessment of risk factors for falls.

Risk Factor	Assessment
History of falls [16,17,18]	Number of falls, consequences, circumstances Falls risk score
Feet changes and footwear [19,20]	Michigan Neuropathy Screening Instrument Manchester Index Footwear questionnaire
Cognitive changes [21,22,23,24,25]	Addenbrooke Cognitive Examination (total score, Mini-Mental State Examination, domains scores, Clock Drawing test, fluency verbal test) Brief Cognitive Screening Battery Digit Span Dual task test (Timed up and Go test associated with fluency task, fNIRS) Memory complaint Social Cognition
Depression and anxiety [26,27]	Geriatric Depression Scale Geriatric Anxiety Inventory
Fear of falling [28]	Falls Efficacy Scale—International
Vitamin D deficiency [29]	Blood test
Acute or chronic conditions (osteoporosis, urinary incontinence, cardiovascular disease, dizziness or cerebellar dysfunctions and others) [30]	Presence of morbidities Cardiac frequency Blood pressure
Living alone and other social issues [31]	If they live alone WHODAS 2.0 Social Support Survey
Use of medications [32]	Dose, frequency, and time of each medication, use of psychotropic drugs
Nutritional deficiency [33]	Body mass index Nutritional condition Blood test (calcium, B12 vitamin, K2 vitamin) Mini Nutritional Assessment
Postural hypotension [34]	Symptoms Drop in blood pressure after changing position
Vision and hearing changes [35,36]	Use of bifocal or multifocal glasses Jaeger Eye Chart Difficulty of hearing or people think you have poor hearing Whisper test
Home safety [37]	Home Fast
Use of walking devices and functional activities [38,39]	Use of walking devices Lawton & Brody scale EuroQol-5D Fall to the floor and get up test
Pain [40,41,42]	Brief Pain Inventory Geriatrics Pain Measure
Muscle strength, mobility, gait, and postural balance [43,44,45]	Timed Up and Go test (simple and dual task) Frailty Assessment Short Physical Performance Battery (balance, gait speed, sit-to-stand test) Sarcopenia Assessment Ankle mobility

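### The effectiveness test for categorical risk factors does not use the baseline status that the trial collects, which costs precision but not validity

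*Protocol article*

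**What the plan says.** In the protocol article, section 2.9 (Statistical Analysis) gives the effectiveness test for categorical outcomes: "To verify the effectiveness of the interventions, the chi-square association test will be used for categorical variables". No baseline covariate, stratification or repeated-measures element goes with it. The same section treats quantitative outcomes differently: "For quantitative variables, the two-way ANOVA test will be used to verify the interaction between groups and evaluations".

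Section 2.6 makes risk factors primary: "Primary outcome measures include falls data and potentially modifiable risk factors for falls". Table 1 lists them. Most are scored scales, but some items are categorical on their face: walking-device use, psychotropic drug use, living alone, and "Use of bifocal or multifocal glasses".

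Section 2.5 shows that baseline status will be on file: "The assessment will be performed at baseline, after 16 weeks of intervention, after 6-month follow-up, and after 12-month follow-up".

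Nothing else in the article fills the gap. Section 2.8 describes 1:1 randomization in blocks of 2, 4 and 6 and states no stratification, so arm sizes are balanced but risk-factor status is left to chance. Mixed-effects models appear at the end of section 2.9 only as a sensitivity analysis for missing data. The other chi-square test in that section compares clinical and sociodemographic characteristics between groups and adjusts nothing.

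**The concern.** Whether a person uses a walking aid or takes a psychotropic drug now is often a good guide to whether they will in 16 weeks. When baseline predicts follow-up in this way, a comparison that ignores it carries avoidable noise.

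Two things are at stake. One is power in a trial of 60 people. The other is interpretation: if one arm happens to start with more affected people, part of that gap reappears at 16 weeks and can look like a treatment effect or hide one. The plan avoids this for its quantitative primary outcomes but not for its categorical ones.

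**Working it through.** **The plan's own figures.** Section 2.3 gives no power or sample size for a categorical risk factor. Its figures rest on ANOVA and on a regression rule: "an effect size of 0.25, a minimum of 28 people should constitute the total sample", then 50, then 60.
- 28: reproduced by the repeated-measures interaction with f = 0.25, α = 0.05, two groups, three measurements, correlation 0.5 and sphericity (power 81.2%). The last three are assumptions.
- 50: 10 / 0.20 = 50.
- 60: 50 × 1.2 = 60.

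The check therefore uses 30 per arm (60 / 2, all randomized) and 24 per arm (30 × 0.8, after the 20% loss). α is two-sided 0.05; the sidedness is an assumption.

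**Tests compared.** Let y be the number affected at follow-up in each arm of size n, and p the pooled proportion.
- Plain chi-square: (y_C/n − y_I/n)² / [p(1 − p) × 2/n].
- Cochran-Mantel-Haenszel (CMH), with strata s = affected or not at baseline: [Σ(a_s − m_s n_Cs/T_s)]² / Σ[m_s(T_s − m_s) n_Cs n_Is / (T_s²(T_s − 1))]. Here a_s is the number affected among controls, m_s the number affected in both arms, and T_s the stratum size.

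The documents give no prevalence or persistence, so every rate below is assumed. Results come from 20,000 simulated trials per setting and repeat to within about one point.

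**Check 1: persistence and onset, 24 per arm.** Follow-up prevalence = baseline prevalence × persistence + (1 − baseline prevalence) × onset. In the first row: 0.6 × 0.85 + 0.4 × 0.10 = 0.55 in control, and 0.6 × 0.45 + 0.4 × 0.10 = 0.31 in the Intervention Group.

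| Baseline prevalence | Persistence, control / intervention | Onset, control / intervention | Chi-square power | CMH power |
|---|---|---|---|---|
| 0.6 | 0.85 / 0.45 | 0.10 / 0.10 | 42% | 52% |
| 0.5 | 0.85 / 0.45 | 0.10 / 0.10 | 31% | 41% |
| 0.5 | 0.85 / 0.40 | 0.10 / 0.05 | 46% | 62% |
| 0.4 | 0.90 / 0.45 | 0.05 / 0.05 | 28% | 45% |
| 0.5 | 0.70 / 0.40 | 0.20 / 0.20 | 19% | 20% |
| 0.5 | 0.60 / 0.30 | 0.30 / 0.20 | 31% | 31% |
| 0.5 | 0.85 / 0.65 | 0.10 / 0.10 | 12% | 15% |

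The gain is 10-17 points in the first four rows and 0-3 in the last three. With no effect (0.5; 0.85 / 0.85; 0.10), rejection is about 5.9% for chi-square and 4.4% for CMH.

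**Check 2: within-person correlation.** Baseline prevalence 40%, follow-up 50% against 25%. Chi-square power is about 45% at 24 per arm and 52% at 30 per arm.

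| Correlation | CMH, 24 per arm | CMH, 30 per arm |
|---|---|---|
| 0 | 44% | 52% |
| 0.3 | 46% | 55% |
| 0.5 | 53% | 64% |
| 0.6 | 61% | 71% |

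Across the rates tried, adjustment costs up to about 2 points at correlation 0. It gains about 1-4 points at 0.3, 8-13 at 0.5 and 16-20 at 0.6. At 0.5 with 30 per arm, the SD of the risk difference falls from 0.121 to 0.106, a variance ratio of (0.106 / 0.121)² = 0.77.

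**Check 3: chance imbalance.** At 50% prevalence, a baseline gap of 15 points or more in either direction occurs in about 31% of trials with 24 per arm and 25% with 30. With no true effect, the expected carry-over is gap × (persistence − onset); for example, 0.15 × (0.85 − 0.10) = 0.11. In simulation at correlation 0.5, among null trials with a gap of at least 15 points in one direction, the unadjusted difference averages +0.10 (30 per arm) to +0.11 (24 per arm). After adjustment it averages about 0. With a true difference of −0.25 and 30 per arm, the averages are −0.15 unadjusted and −0.25 adjusted.

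**The case against.** The best defence is that this is a matter of efficiency. Under randomization the plain comparison is unbiased on average, and chance imbalance is already counted in its error rate: 5.9% at 24 per arm and 5.2% at 30 in the null simulations. That stands. A reader might infer that the test is invalid or biased, and the documents do not support this.

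A reader might also infer that small expected counts make the chi-square approximation harmful here. How often they occur depends heavily on the assumed rates, and at 20% prevalence with 24 per arm the chi-square type I error stayed at about 5%. Sparse cells matter more for the adjusted analysis, because stratifying makes them smaller.

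The size of the loss depends on persistence and effect size, which the documents do not give; the lower rows of check 1 show it can vanish. Not every item in Table 1 is affected either. A fall in blood pressure may be analysed as a quantity, and memory complaint has no stated scale. The sample size rests on motor risk factors, many of them scored. The categorical items are thus only part of the primary outcome.

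Finally, a condensed article may leave covariates to a fuller plan, and the tabulated category could be improvement rather than follow-up status. The article says neither. It names the test and mentions baseline only for the quantitative outcomes, so the point survives as a request to state the adjustment.

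**Conclusion.** The concern holds as a cheap improvement in precision. The article fixes an effectiveness test for categorical primary risk factors that makes no stated use of baseline status, although that status is collected and the quantitative outcomes use theirs.

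At 24 to 30 per arm the power given up is about 0 points when baseline is weakly predictive, and about 10-20 points when 85-90% of affected controls remain affected and the effect is large. Chance imbalance of 15 points or more would arise in roughly a quarter to a third of trials for a factor with 50% prevalence, and at a within-person correlation of 0.5 would shift the unadjusted estimate by about 10 points on average. All of this rests on assumed prevalence, persistence and effect. None of it makes the planned test wrong.

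**What to change.** In section 2.9, replace the chi-square sentence for effectiveness with one that does the following:
- For each binary risk factor, compare the arms at 16 weeks by logistic regression, or by a Cochran-Mantel-Haenszel test, adjusted for the same factor's baseline status.
- Report the effect with a 95% confidence interval.
- Use a penalised or exact version when cells are sparse.
- Keep the plain chi-square as descriptive.

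It would help to list which Table 1 items will be analysed as categorical. A repeated-measures logistic model could extend the comparison to 6 and 12 months.

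The change needs no new data or participants. It costs slightly more analysis work, and up to about 2 points of power for a factor whose baseline status is not predictive.

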To address missing data resulting from loss to follow-up, we plan to use multiple imputation methods under the assumption of missing at random and to perform sensitivity analyses using mixed-effects models, which can accommodate unbalanced data and account for intra-individual variability over time. These approaches will help to minimize potential bias associated with missing outcome data.

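### The 28-person figure rests on a repeated-measures calculation with unstated inputs, while Sections 2.3 and 2.9 name only a two-way ANOVA with no within-participant term

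*Protocol article*

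**What the plan says.** Section 2.3 of the protocol article describes the sizing test as "two-way ANOVA, considering group and time effects, with Bonferroni test to control type I error due to multiple primary outcomes". Its stated aim is "the purpose of identifying the effectiveness of risk factors after 16 weeks of intervention". With 5% type I error and 80% power it concludes: "an effect size of 0.25, a minimum of 28 people should constitute the total sample". It gives neither the number of measurements per person nor the correlation between them. The recruitment target of 60 comes from a separate rule for the regression analyses (50 people), raised for 20% loss.

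Section 2.5 schedules four assessments of each participant: baseline, 16 weeks, and the 6-month and 12-month follow-ups.

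Section 2.9 names the effectiveness analysis for quantitative variables: "the two-way ANOVA test will be used to verify the interaction between groups and evaluations". Simple main effects follow only if an interaction is found. In its closing paragraph, on loss to follow-up, it plans multiple imputation and "sensitivity analyses using mixed-effects models, which can accommodate unbalanced data and account for intra-individual variability over time".

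**The concern.** The same people are measured up to four times, so their values are correlated. A two-way ANOVA with group and evaluation as its only factors has no participant term, and its error variance contains the differences between people. A repeated-measures or mixed model removes those differences from the group-by-evaluation test. The two analyses give different p-values from the same data, and software offers both under similar names.

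The article names the test twice without the within-participant term. It also prints a sample size that only the repeated-measures version can produce. A reader therefore cannot recover the inputs behind 28, and an analyst who follows the text literally would run a much weaker test on the primary quantitative outcomes than the one used for sizing.

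**Working it through.** **Inputs.** From Section 2.3: effect size 0.25 (taken as Cohen's f), alpha 0.05 undivided as printed, power 0.80, N = 28. From Sections 2.1 and 2.8: two groups, 1:1. From Section 2.5: up to m = 4 measurements. The stated 16-week purpose implies m = 2 (baseline and 16 weeks). The within-person correlation ρ is not in the article and is an assumption throughout.

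**1. Reproducing 28.** For the repeated-measures group-by-time interaction, λ = f²·N·m/(1 − ρ), with m − 1 and (N − 2)(m − 1) degrees of freedom (equal correlations assumed). At N = 28:

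| m | ρ | λ | Power at 28 | Smallest even N for 80% |
|---|---|---|---|---|
| 3 | 0.5 | 0.0625·28·3/0.5 = 10.5 | 81.2% | 28 |
| 2 | 0.6 | 0.0625·28·2/0.4 = 8.75 | 81.3% | 28 |
| 4 | 0.4 | 0.0625·28·4/0.6 = 11.67 | 80.8% | 28 |
| 2 | 0.5 | 0.0625·28·2/0.5 = 7.0 | 72.1% | 34 |
| 4 | 0.5 | 0.0625·28·4/0.5 = 14.0 | 87.9% | 24 |

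So 28 reproduces, but from at least three different input pairs. With two measurements it needs ρ of about 0.6.

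**2. The test as named.** For the ordinary two-way ANOVA interaction, λ = f²·(N·m), with m − 1 and N·m − 2m degrees of freedom. At m = 2 and N = 28, λ = 0.0625·56 = 3.5 and power is 45%. At N = 64, λ = 0.0625·128 = 8.0 and power is 80%. The smallest N for 80% is 64, 53 and 45 at m = 2, 3 and 4 (54 and 46 if the groups must be equal). None of these is 28.

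**3. The named test on correlated visits.** The formula in step 2 assumes independent observations, so the test was simulated on correlated data (20,000 trials per setting). With m = 2, ρ = 0.5 and f = 0.25:

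| N | Literal two-way ANOVA | Repeated-measures test |
|---|---|---|
| 28 | about 43% | 72% |
| 48 (= 60 × 0.8) | about 74% | 92% |
| 60 | about 85% | 97% |

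The true type I error of the literal interaction test is about 0.7% instead of 5%. The reason is that, with no effect, the interaction mean square has expectation σ²(1 − ρ) while the error mean square has about σ². At ρ = 0.5 the F ratio is therefore about half what it should be.

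With four visits the loss is smaller at the planned size: the literal test has 83% power at 48 by the formula, and about 85% in simulation at ρ = 0.4.

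**The case against.** The strongest reply is that a group-by-time "two-way ANOVA" is common shorthand for a mixed or repeated-measures ANOVA. Both sections use the same term, and 28 reproduces only under the repeated-measures reading, so sizing and analysis may well agree in intent. That stands. A reader might infer that the trial will treat one person's visits as independent; the article never says so.

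The sensitivity analysis should not be over-read either. The mixed-effects models appear in a paragraph on missing data, and a repeated-measures ANOVA would also handle within-person correlation. Their placement does not prove that the main analysis ignores it.

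A reader might also take 43% against 80% as the trial's power deficit. That does not hold. The 43% belongs to 28 people, two visits and the literal test; in that setting the repeated-measures test itself reaches only 72%, and the trial plans 60. Likewise, a literal ANOVA would inflate false positives for the overall group effect (about 11% with two visits at ρ = 0.5), but Section 2.9 rests effectiveness on the interaction, where the error is conservative.

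Finally, a condensed article may leave the error structure to a fuller document. What remains is that this article chose to print both a test name and a sample size, and taken as written they do not match.

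**Conclusion.** The point holds as a mismatch between what is named and what was calculated; it does not establish that a wrong analysis is intended. The figure of 28 belongs to a repeated-measures test whose number of measurements and correlation are not given. For the stated 16-week comparison, 28 is right only if the correlation is about 0.6; at 0.5 the figure is 34.

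If the text were followed literally, the cost at the planned size would be moderate. With two visits and correlation 0.5, power would be about 74% instead of 92% among 48 completers, and the interaction test would run at about 0.7% instead of 5%. With four visits, power at 48 would still exceed 80%. These figures assume f = 0.25, equal correlations and a 5% test. The change is worth making because the consequence falls on primary outcomes and wording alone removes it.

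**What to change.** In Section 2.9, make the main analysis of quantitative outcomes a model with evaluation as a within-participant factor. The mixed-effects model already planned as a sensitivity analysis serves: group, evaluation, their interaction, and correlated errors within participant. It also copes with unbalanced data. A repeated-measures ANOVA named as such would remove the ambiguity too, but the mixed model is already in the plan.

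In Section 2.3, name the repeated-measures group-by-evaluation interaction as the test behind 28, and state the number of measurements and the correlation. If the 16-week comparison with two measurements and those inputs does not give 28, restate the figure (34 at correlation 0.5).

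The cost is wording in two sections. No extra data or participants are needed, and the enrolment target of 60 is unaffected, because the regression rule sets it.

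### Single-step Bonferroni across the primary outcomes is valid, but Holm's step-down gives the same error control and never less power: an optional, modest gain

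*Protocol article*

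**What the plan says.** Section 2.9 (Statistical Analysis) of the protocol article analyses quantitative variables by two-way ANOVA, "with Bonferroni test to control type I error due to multiple primary outcomes". For the next step it says: "If an interaction is identified, simple main effects analyses will be performed, with adjustments for multiple comparisons (Bonferroni"). Section 2.3 names the same correction in the sample size assumptions: "two-way ANOVA, considering group and time effects, with Bonferroni test to control type I error due to multiple primary outcomes". No step-down or other variant is mentioned, so ordinary single-step Bonferroni is the natural reading.

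Three other statements bear on the size of the effect:

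- Section 2.9 sets the level: "A significance level of α = 0.05 will be adopted for all analyses".
- Section 2.6 defines the family only in general terms: "Primary outcome measures include falls data and potentially modifiable risk factors for falls". Table 1 lists those risk factors in 16 rows. The number of tests that share the correction is not given.
- Section 2.3 plans 60 participants and allows for a loss of 20%.

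**The concern.** Single-step Bonferroni holds every test to alpha divided by the full number of tests, even after some null hypotheses have been rejected. Holm's procedure orders the p-values and relaxes the divisor after each rejection. It keeps the same family-wise error under any dependence between outcomes. For hypothesis testing, then, Bonferroni gives up some power and gains nothing in error control.

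The setting makes this worth a look. The trial is small and its primary outcomes cover a broad set of risk factors. The intervention is meant to act on all the modifiable risk factors found in each person, and benefit on many outcomes at once is the situation in which a step-down procedure helps most. What is at stake is the chance of confirming individual risk-factor effects that are real.

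**Working it through.** **Inputs**

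- From the article: total 60, allocation 1:1, loss 20%, alpha 0.05, effect size 0.25, 16 rows in Table 1. Completers: 60 × 0.8 = 48, or 24 per arm.
- Assumed, because not stated: number of tests M (16 in the main example), share of true effects (25%, 50%, 75%), correlation 0.3 between test statistics, two-sided tests, effects of 0.5 and 1.0 SD.

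**The plan's own figure.** Section 2.3 gives "4) type I error at 5%; (5) statistical power at 80%; and (6) an effect size of 0.25, a minimum of 28 people". Take a repeated-measures within-between interaction with f = 0.25, three measurements and within-person correlation 0.5 (the last two assumed). Then lambda = f² × N × measurements / (1 − correlation) = 0.0625 × 28 × 3 / 0.5 = 10.5, with 2 and 52 degrees of freedom. At an undivided alpha of 0.05 the power is 0.812, so 28 is reproduced. The inputs are not uniquely identified: four measurements at alpha 0.025 also give 28.

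**The two rules with M = 16**

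- Bonferroni: every p-value is compared with 0.05/16 = 0.003125.
- Holm: the smallest p-value is compared with 0.05/16, the next with 0.05/15 = 0.00333, and so on. After eight rejections the threshold is 0.05/8 = 0.00625.

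Each Holm threshold is at least the Bonferroni threshold, so no Bonferroni rejection can be lost. The first step is identical, so the chance of at least one rejection is the same by construction.

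**Closed-form check of Bonferroni.** The noncentrality is d × √(24/2), which is 3.46 for 1.0 SD and 1.73 for 0.5 SD. The two-sided critical value at 0.05/16 is 2.955. Power is Φ(3.46 − 2.955) = 0.69 and Φ(1.73 − 2.955) = 0.11.

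**Simulation.** Equicorrelated normal test statistics, correlation 0.3, M = 16, 24 per arm. Average power per true effect:

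| Effect | Share true | Bonferroni | Holm | Gain (points) |
|---|---|---|---|---|
| 0.5 SD | 25% | 11.1% | 11.3% | 0.2 |
| 0.5 SD | 50% | 11.0% | 11.6% | 0.6 |
| 0.5 SD | 75% | 11.1% | 12.2% | 1.1 |
| 1.0 SD | 25% | 69.4% | 70.8% | 1.4 |
| 1.0 SD | 50% | 69.7% | 73.5% | 3.8 |
| 1.0 SD | 75% | 69.5% | 76.7% | 7.2 |

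Holm's family-wise error was at most 4.7%, and no Bonferroni rejection was dropped in any run. The chance of detecting at least one true effect differed by 0.1 point or less.

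**Which effect size fits the plan?** Under an interaction test with two measurements, within-person correlation 0.5 and 48 completers, f = 0.25 gives lambda = 0.0625 × 48 × 2 / 0.5 = 12. Its square root is 3.46, the same noncentrality as 1.0 SD above. Under the simple two-group conversion d = 2f, the effect is 0.5 SD. The article does not settle which applies, so both are shown.

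**Extremes.** With all 60 analysed, f = 0.25 (two measurements, correlation 0.5) and uncorrelated outcomes, five tests with one true effect give 90.3% against 90.4%. If all 16 of 16 effects were true, the figures are 82.1% against 95.0%.

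**Comparison with the choice of family.** With 48 completers, three measurements and correlation 0.5, single-outcome power under Bonferroni is 0.97 for M = 1, 0.89 for M = 5, 0.80 for M = 16 and 0.71 for M = 40. Going from one outcome to 16 costs 17 points and to 40 costs 26. The main table shows Holm returning at most about 7.

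**The case against.** The strongest reply is that nothing here is wrong. Bonferroni is valid under any dependence and errs on the safe side, so no conclusion of the trial would be biased by it. It also provides simple simultaneous intervals that match its tests (with 16 outcomes, each at 1 − 0.05/16 = 99.69%). Holm has no equally simple counterpart. Unadjusted 95% intervals beside Holm-adjusted p-values can exclude zero while the adjusted test is not significant. That matters in a trial that also studies minimal clinically important differences, where readers will look at effect sizes. This stands: it makes the change optional and means unadjusted intervals must be labelled.

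The reply also says the larger gains need many sizeable effects beyond an active exercise comparator. That stands too: the 7-point figure needs three quarters of the outcomes to differ by about 1 SD.

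It does not follow that the remark is empty. The method is named in the article rather than left to an unseen plan, and Holm is never worse for testing.

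A reader might infer that real effects are being thrown away for nothing. The documents do not support that. The loss is close to zero when few effects are real, the chance of some finding is unaffected, and Bonferroni buys simpler intervals. Nor should a reader infer that Holm would repair the trial's multiplicity problem. Holm needs a declared number of tests just as Bonferroni does, and its first step uses the same divisor.

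**Conclusion.** The planned correction is valid but never more powerful than Holm's step-down, which has the same family-wise error control. Adopting Holm is a cheap, optional efficiency gain of about 0.2 to 1 point per true effect at 0.5 SD and about 1 to 7 points at 1.0 SD. Those figures assume 16 outcomes, 24 per arm, correlation 0.3 and 25% to 75% of effects true. None of these is fixed by the article except that 24 per arm follows from its planned total and loss. The mathematical ordering of the two methods is certain; the size of the gain is not. Two weightier matters remain whichever method is used: the family of primary outcomes is not declared, and the sample size is stated at 5% with no divisor although a correction is named.

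**What to change.** In section 2.9, and for consistency in section 2.3, replace Bonferroni by wording such as: Holm step-down, family-wise alpha 0.05, applied to the declared family of primary outcomes. Make the same replacement for the simple-effects comparisons. Do this before any data by group are seen. Report Holm-adjusted p-values, and label any unadjusted 95% confidence intervals as unadjusted.

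The cost is a change of wording and a sort of the p-values; participants, visits and budget are unaffected. The one real downside is that simultaneous intervals matched to the tests become less simple. If the sponsor values such intervals more than the extra power, keeping Bonferroni is defensible.

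The edit in section 2.3 does not alter or explain the figure of 28. Declaring the family and reconciling the sample size with the correction must be done separately.
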